Moreover, few authors have investigated the effects of cessation of exercise [45,46]. Mujika & Padilla [46] argue that detraining can be divided into two study periods: short-term, less than 4 weeks, and long-term, more than 4 weeks. Therefore, Toraman & Ayceman [47] found that after 4 weeks of interruption following a 9-week aerobic, strength, and flexibility training program, conducted 3 times a week, participants showed a reduction in performance levels on various functional tests, standing out the Chair Sit and Reach, compared to the end of the intervention, although the changes were not statistically significant. Thus, the impact of aquatic exercise, core stability exercise, and trunk and lower limb stretching cessation on individuals with CLBP remains unclear.

This trial aims to assess the effect of a combined aquatic and land-based exercise program compared to an aquatic program on pain, functional disability, and quality of life in adults with CLBP. Secondary objectives include investigating the effects on lumbar mobility and fear of movement, as well as the impact of training cessation on these variables 4 weeks after the end of the intervention. We hypothesize that combined aquatic and land-based exercise decreases significantly pain, and functional disability, and increases quality of life in adults with CLBP.

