### Participants

The study sample will consist of both gender Portuguese participants, over 18 years, with CLBP lasting three months or longer and with an intensity of 3 or higher on the visual analogue scale (VAS) at rest. Individuals who refuse to participate or do not provide informed consent will be excluded, as well as those with pain radiating to the lower limb, recent pregnancy or childbirth (less than 8 weeks ago) [50], ongoing physical therapy treatments, severe rheumatological, neurological, neoplastic, cardiovascular diseases, or other conditions that could prevent full participation in the intervention, a history of spinal surgery, inflammatory, infectious, or malignant spinal diseases, and psychiatric disorders that may affect adherence and symptom assessment [41–43].

The sample will be randomly divided into two groups: the experimental group, which will undergo the aquatic and land-exercise program (ALG), and the control group, which will perform the aquatic-exercise program (AG).

The required sample size was calculated using the G*Power software (3.1.9.4; Heinrich Heine University Düsseldorf, DE), based on a study with 65 participants by Dundar *et al*. [42] and corroborated by other studies [51–53]. The aim was to detect differences in pain intensity (VAS) between the aquatic exercise program group and the control group (land exercise), with an effect size of 1.079, α=0.05, and a power of 80%. The total sample size needed to achieve the objective will be 30 participants (15 in each group).

Thus, the study should start with an additional 15% of the planned sample size for each group to account for potential dropouts and as well as adopt cognitive-behavioral strategies to reduce dropout rates, such as setting flexible and participant-driven goals or providing positive and individualized feedback [54,55].

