#### Randomization and Blinding.

Participants who meet eligibility criteria will be given an alphanumeric code to maintain data confidentiality and anonymity. Participants will be randomly assigned to either ALG or AG, with a 1:1 allocation. Randomization will be performed by the principal investigator using a block randomization method generated by a computer program to ensure equal sample sizes in both groups. The block size will not be disclosed to maintain concealment. Participants will be informed of their group allocation (ALG or AG) via telephone contact. The principal investigator will not be actively involved in the intervention, data collection or data analysis. Randomization will only be known to the physiotherapists responsible for the intervention and the principal investigator. The examiner will evaluate participants before the intervention and after 8 weeks of intervention, ensuring blinding to group allocation, and participants will be asked not to disclose this information to the examiner. Each intervention will have a physiotherapist responsible for its execution, who will be instructed not to reveal participants’ group allocation to other research team members. Both data collector and data analyst will be unaware of the participants’ group distribution and will also be considered blinded. Only the principal investigator will have full knowledge of the entire research flow.

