### Statistical analysis

An inspection of the data will be made for missing values or univariate outliers. A priori power analysis through ${\text{G}}^{*}$Power (3.1.9.7) [96] and ANOVA repeated measures, within-between interaction will be use to determine the required sample size considering the following input parameters: (effect size *f* = 0.4; α err prob = 0.05; statistical power = 0.95) [97]. Data analyses will be performed using SPSS Statistics version 29.0 (SPSS Inc., IBM Company, Chicago, Illinois, USA). Descriptive statistics (mean ± SD) will be performed for all variables in the analysis. Assuming data normality, a 2×3 within-between interaction factorial ANOVA will be applied for intra and inter group comparisons. To control for Type I errors, multiple comparisons will be adjusted using the Bonferroni correction (i.e., alpha level divided by the number of tests) as suggested by several authors (e.g., Ho, 2014) [98].The magnitude of the global effect size will be calculated using Cohen’s effect size. The Cohen’s *d* effect size is categorized according to the following criteria: *d* = < 0.20 (small), 0.21–0.79 (medium) and > 0.80 (large) [99–101]. Significance level set at ρ
≤ 0.05. Full statistical analysis and results are expected to be completed in May 2025.

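### The 2×3 group-by-time interaction mixes the end-of-programme effect with the cessation question and does not adjust for baseline; a baseline-adjusted ALG-minus-AG contrast at M1 should be named as primary, and the hypothesis should name its comparator

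*Protocol article*

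**What the plan says.** **Analysis.** Under Statistical analysis, assuming normality, "a 2×3 within-between interaction factorial ANOVA will be applied for intra and inter group comparisons". Multiple comparisons are Bonferroni-corrected, but the number of tests is not given. No contrast or time point is called primary, and no baseline adjustment is mentioned. A power analysis in the same section is also aimed at the within-between interaction ("effect size *f* = 0.4; α err prob = 0.05; statistical power = 0.95"), but it reports no sample size.

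**Question.** The aim in the Introduction compares the combined programme with the aquatic one on pain, disability and quality of life. M2 belongs to the secondary objectives: "Secondary objectives include investigating the effects on lumbar mobility and fear of movement, as well as the impact of training cessation". The Discussion puts the open question as whether the extra land session does better at the end of the intervention. The hypothesis, however, reads "We hypothesize that combined aquatic and land-based exercise decreases significantly pain, and functional disability", continues with quality of life, and names no comparator.

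**Size.** Under Participants, the calculation is for one between-group difference in VAS, "with an effect size of 1.079, α=0.05, and a power of 80" per cent, giving 15 per group. Each group is enlarged by 15% for dropout. Allocation is 1:1.

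**The concern.** The test named in the analysis section is not the test that the aim and the sample size imply. A 2-df interaction asks whether the two arms have different profiles over M0, M1 and M2. It can be significant because the arms part only after the programme ends. It can also miss an M1 effect that partly fades by M2. Because M0 enters as a repeated outcome, the analysis does not use it as a covariate to sharpen the M1 comparison, although it is collected on everyone.

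The wording of the hypothesis adds a risk of interpretation. Both arms receive active exercise and everyone enters with a resting VAS of at least 3, so improvement in both arms is plausible. Within-group comparisons are planned, and a pre-post change in ALG would fit the hypothesis as written while saying nothing about ALG against AG.

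At stake are power in a small trial and clarity about which result answers its question.

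**Working it through.** **Inputs.** From the protocol: n = 15 per arm, 1:1, α = 0.05, d = 1.079, visits M0, M1 and M2. Assumed, because the protocol does not give them: two-sided testing, SD 1 at each visit, equal correlation ρ between visits (0.3, 0.5, 0.7, with 0.9 as an extreme), and the share r of the M1 effect still present at M2 (0, 0.5, 1). A smaller effect, d = 0.8, is added for illustration.

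**1. The plan's own figure.** Two-sample t-test, noncentrality d·√(n/2) = 1.079 × √7.5 = 2.955 on 28 df: power 81.4%. So 15 per group reproduces exactly, as a single between-group comparison and not as a 2-df interaction.

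**2. Interaction.** With arm differences (0, d, r·d) at the three visits:

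λ = (n/2)·d²·[1 + r² − (1 + r)²/3] / (1 − ρ), on 2 and 56 df.

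The bracket is 2/3 at r = 0, 1/2 at r = 0.5 and 2/3 at r = 1. So r = 0.5 is the pattern least favourable to the interaction, and both ends have to be shown as well.

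**3. M1 difference adjusted for M0 (ANCOVA).** λ = (n/2)·d² / (1 − ρ²), on 1 and 27 df.

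**4. Example, d = 0.8 and ρ = 0.5.**
- ANCOVA: 7.5 × 0.64 / 0.75 = 6.40.
- Interaction, r = 0.5: 7.5 × 0.64 × 0.5 / 0.5 = 4.80.
- Interaction, r = 0 or 1: 7.5 × 0.64 × (2/3) / 0.5 = 6.40, the same λ as ANCOVA but spread over two degrees of freedom.

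**5. Power** (20,000 simulated trials per scenario; the interaction formula agrees to within about a point). The lower interaction figure is for r = 0.5, the upper for r = 0 or 1.

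| d | ρ | ANCOVA at M1 | 2×3 interaction |
|---|---|---|---|
| 0.8 | 0.3 | 58% | 35–45% |
| 0.8 | 0.5 | 67% | 47–59% |
| 0.8 | 0.7 | 83% | 69–82% |
| 1.079 | 0.3 | 84% | 58–71% |
| 1.079 | 0.5 | 90% | 73–85% |
| 1.079 | 0.7 | 97.5% | 92–98% |

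**6. Where the gain ends.** The ratio of ANCOVA λ to interaction λ is 1.5/(1 + ρ) at r = 0 or 1, and 2/(1 + ρ) at r = 0.5. The second ratio always exceeds 1. The first falls below 1 once ρ exceeds 0.5, and the single degree of freedom then offsets it only up to about ρ = 0.7, where the tests tie. At ρ = 0.9 and d = 0.5 the interaction is ahead, 88% against 85%.

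**7. Arms that differ only at M2.** With no M1 difference, 0.8 SD at M2 and ρ = 0.5, the interaction rejects in 59% of trials and the M1 ANCOVA in 5%. A significant interaction alone therefore does not locate the effect at M1.

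**8. Within-ALG change.** If both arms improve equally by 0.8 SD with ρ = 0.5, the SD of change is √(2 × 0.5) = 1. The noncentrality is 0.8 × √15 = 3.10 on 14 df, and an unadjusted paired test in ALG is significant about 82% of the time. With an equal improvement of 0.5 SD, exactly one of the two arms is significant in 49% of trials.

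**The case against.** A 2×3 mixed ANOVA is a valid analysis of this design, and choices such as covariates, a mixed model or the handling of a missed visit are commonly left to a statistical analysis plan that is not shown. This stands in part. Complete-case deletion, for instance, is how classical repeated-measures ANOVA usually works, but the protocol does not state it, so no weight is put on it here. What the article does fix is the interaction test, without saying which contrast answers the aim.

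The planned inter-group comparisons could also supply an M1 contrast. That is true, but it is not named as primary and is not baseline-adjusted. At d = 1.079 an unadjusted M1 comparison has about 81% power, or about 66% if Bonferroni is spread over three visits (an assumption).

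Four stronger readings are tempting, and the document does not support them:
- *The hypothesis concerns ALG alone.* One sentence lacks a comparator; the aim and the Discussion are comparative.
- *The trial can declare success on a within-group change.* No success rule is stated. With equal improvement in both arms the interaction rejects at about its nominal 5%. The 82% belongs to an unadjusted paired test that the plan does not name, and it shows a risk of misreading only.
- *The 59% is a false-positive rate.* In that scenario the arms truly diverge, and cessation is a stated objective.
- *The adjusted contrast always has more power and costs nothing.* It ties or trails in the patterns in step 6 of the working. At ρ = 0.1 with the effect fully kept at M2, the ANOVA group main effect is ahead at d = 1.079 (85% against 80%). A change now also has procedural costs.

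**Conclusion.** The point holds as a mismatch between question and test. The interaction does not isolate the M1 difference between arms, the baseline score is not used for adjustment, and the hypothesis sentence should carry its comparator. That M1 is primary is an inference from the aims, the Discussion and the single-contrast sample size; the protocol does not say so outright.

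For ρ between 0.3 and 0.7, moving to the adjusted M1 contrast gains from about 1 to 24 percentage points at d = 0.8, and from nothing to about 26 points at d = 1.079. The largest gains occur at low ρ with half the effect kept at M2. These sizes rest on assumed correlations, compound symmetry and the assumed M2 pattern. The mismatch itself does not depend on them.

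**What to change.** - **Primary analysis:** for each primary outcome (VAS, ODI, SF-36), the ALG-minus-AG difference at M1 adjusted for the M0 score, with a 95% confidence interval, by ANCOVA or by a linear mixed model on all available visits.
- **Secondary:** a pre-specified ALG-minus-AG contrast at M2 for the cessation question.
- **Within-arm changes:** descriptive only.
- **Hypothesis:** restate it as ALG compared with AG at M1 for pain, disability and quality of life, so that none of the three primary domains is lost.

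No extra participants or visits are needed, and SPSS, the named software, can fit these models. The costs are one degree of freedom for the covariate, a separate M2 contrast to specify, and a dated amendment. Recruitment began in September 2024 and data collection in November 2024, so the change has to be recorded before any unblinded analysis.

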#### Data Collection.

After enrollment, participants will complete three evaluation phases: before the intervention (M0), after the intervention (M1), and 4 weeks after the end of the intervention (M2). Data collection started in November 2024 and is expected to be completed in April 2025. During data collection, participants will start each data collection session by filling out the questionnaires (Oswestry Disability Index, MOS Short Form Health Survey 36 Item, and Tampa Scale of Kinesiophobia-13) and the Visual Analog Scale for pain at rest, during movement, and at night, which will take approximately 30 minutes. Following this, the physiotherapist responsible for the assessment will measure weight and height, and then assess lumbar spine mobility using the Modified-Modified Schober Test, taking the best of three measurements. To standardize data collection, each participant will be asked to stand barefoot on a paper where the outline of their feet will be drawn to ensure consistent positioning across all measurements. This procedure will be repeated three times, with a 30-second break between repetitions. Participants will be instructed to place their feet at hip-width apart and their upper limbs relaxed along the body in the test starting position [68,69]. Fig 2 shows the study design with key moments of the intervention and data collection.

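### Free improvement: the 2×3 ANOVA makes the baseline score an outcome level; adjusting the between-arm comparison for M0 would usually be more precise and remove its exposure to chance baseline imbalance

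*Protocol article*

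**What the plan says.** The only inferential model named in the article is in Statistical analysis: "a 2×3 within-between interaction factorial ANOVA will be applied for intra and inter group comparisons". Under Data Collection the assessments are "before the intervention (M0), after the intervention (M1), and 4 weeks after the end of the intervention (M2"), and there are no others. The three-level factor is therefore M0, M1 and M2.

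The same section adds that "multiple comparisons will be adjusted using the Bonferroni correction". It names no covariate, ANCOVA or baseline-constrained model. Under Randomization and Blinding, allocation uses a "block randomization method generated by a computer program to ensure equal sample sizes in both groups", which balances numbers and not baseline scores; no stratification is mentioned.

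The sample size under Participants was obtained "with an effect size of 1.079, α=0.05, and a power of 80"%, and "The total sample size needed to achieve the objective will be 30 participants (15 in each group"). Recruitment is to start with "an additional 15% of the planned sample size for each group to account for potential dropouts", so 15 per arm is the number meant to remain for analysis.

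**The concern.** The trial's main question is whether the combined programme does better than the aquatic programme alone. The 2×3 ANOVA offers three readings of that question, and none conditions on the participant's own starting score:

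- The group main effect averages in M0, where no treatment effect can exist.
- The group-by-time interaction rests on changes from M0, which carry all the noise of the M0 measurement.
- A Bonferroni-adjusted post hoc comparison of the arms at M1 ignores M0.

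M0 is to be measured on every participant for every outcome. With 15 per arm and no balancing on baseline, leaving it out as a covariate gives up precision in a trial sized at only 80% power. It also lets a chance baseline difference move the estimate.

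**Working it through.** **Inputs.** From the protocol: 15 per arm, standardised difference 1.079, α = 0.05, power 80%, VAS MCID 20 mm. Assumed, because the protocol gives no figure: M0–M1 correlation r = 0.3, 0.5, 0.7; equal SDs at all visits; equal correlation between every pair of visits; two-sided testing without Bonferroni adjustment. The second power statement ("α err prob = 0.05; statistical power = 0.95", with f = 0.4) gives neither a correlation nor a sample size, so r cannot be recovered from it.

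**1. The plan's own figure.** A two-sample t-test (noncentral t) at d = 1.079 and 15 per arm has 81.4% power; 14 per arm gives 78.5%. The stated 30 reproduces with a two-sided test.

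**2. Precision of a single-visit contrast,** in units of SD² before the common factor 2/15:

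- Raw M1: 1.
- Change M1−M0: 2(1−r).
- ANCOVA of M1 on M0: (1−r²) × (1+1/26), the last factor being the cost of estimating the slope at 15 per arm.
- ANCOVA relative to change: (1+r)/2 × 27/26 = 0.675, 0.779, 0.883 at r = 0.3, 0.5, 0.7. The variance is thus about 32%, 22% and 12% smaller.
- ANCOVA beats raw M1 only if r² > 1/27, that is r > 0.19. It beats change only if r < 52/27 − 1 = 0.93.

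Power at d = 1.079, change v ANCOVA: 67% v 83%, 81% v 90%, 96% v 97%.

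**3. Power of the planned test.** The interaction in a 2×3 ANOVA is a 2-df test that also uses M2, so step 2 does not describe it. It was simulated (20,000 trials per setting); ranges cover repeat runs.

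| Effect | Test | r = 0.3 | r = 0.5 | r = 0.7 |
|---|---|---|---|---|
| 1.079 SD at M1 and M2 | 2×3 interaction | 71% | 85–86% | 97–98% |
| | ANCOVA at M1 | 83–84% | 89–90% | 97–98% |
| 0.8 SD at M1, 0.4 SD at M2 | 2×3 interaction | 34–35% | 46–47% | 70% |
| | ANCOVA at M1 | 58–59% | 67–68% | 83% |

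With no effect, both tests reject in about 5% of trials. If the arms were instead compared through the group main effect, power for the sustained effect would be 74%, 65% and 57%. ANCOVA of the M1–M2 mean on M0, which uses both visits as the interaction does, has about 96%, 97–98% and more than 99% for the sustained effect.

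**4. Chance imbalance.** The between-arm difference in mean M0 has SD √(2/15) = 0.37 SD, and it exceeds 0.5 SD in 17% of trials. Given a baseline difference δ, the expected raw M1 difference is the treatment effect plus rδ. The change contrast is therefore off by rδ − δ = −(1−r)δ. For δ = 0.37 SD the size of the shift is 0.26, 0.18 and 0.11 SD at r = 0.3, 0.5, 0.7. ANCOVA is shifted by about 0. At an assumed VAS SD of 20 mm, δ = 0.365 × 20 = 7.3 mm, and the shift is 5.1, 3.7 and 2.2 mm against the MCID of 20 mm.

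**5. Unequal SDs.** Entry requires rest VAS of at least 3, which truncates M0 but not M1. If the M0 SD is 0.8 of the M1 SD (an assumption), the change variance is 1 + 0.64 − 1.6r = 1.16, 0.84, 0.52. Power for change v ANCOVA is then 75% v 83%, 88% v 90%, and 97–98% for both.

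**The case against.** The strongest reply is that this is an efficiency choice and not an error. That stands. The mixed ANOVA is a standard model, has the right size and is unbiased over repeated randomisation. A reader might infer that it gives biased or invalid treatment comparisons. The documents do not support that: the shift in step 4 is conditional on the imbalance that happens to occur, and it averages to zero over randomisations.

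Three other strong readings also fail.

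- ANCOVA does not have the smaller standard error at every correlation. At 15 per arm it loses slightly to raw M1 scores below r of about 0.19, and to change scores above about 0.93.
- The stated 80% power is not shown to be missed. It equals the change-score power at r = 0.5 and is exceeded above that. The 2-df test with a sustained effect does somewhat better still. A shortfall needs a lower r, or an effect that is smaller or fades, and the protocol fixes none of these.
- A baseline gap of, say, 10 mm is not a 10 mm error. The change contrast moves by (1−r) times the gap, which is 3 to 7 mm for r from 0.7 to 0.3.

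Two further points stand in part. The entry threshold may narrow the M0 distribution for rest pain, which removes most of the single-visit gain at r of 0.5 or more. Separate ANCOVAs at M1 and M2 would also leave the cessation objective, stated at the end of the Introduction, without an analysis, so the fix has to provide one.

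A separate analysis plan could add a covariate. But the article itself names the model for between-group comparison, so the point concerns what is written and not an omitted detail.

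**Conclusion.** The point holds as a free improvement that should be made, not as a fault that invalidates the trial. The planned model treats M0 as an outcome, and conditioning on M0 would usually serve the between-arm question better.

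At r = 0.3 to 0.5 the gain over the planned interaction test is roughly 4 to 13 percentage points of power for a sustained effect of 1.079 SD, and about 20 to 25 points for an effect fading from 0.8 to 0.4 SD. At r = 0.7 the single-visit gain is nil if the effect is sustained and about 13 points if it fades. Protection against chance imbalance comes in addition.

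The direction is secure over the correlations one would ordinarily expect. The size is not, because it rests on an undocumented r, on equal SDs and on an assumed course of the effect after the programme ends.

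**What to change.** In Statistical analysis, base the between-group comparison for each outcome on a linear model of the M1 score with group and that participant's M0 score as terms. A mixed model of M1 and M2 with M0 as covariate would also serve, provided that the M1 contrast is named as the main one. Report the adjusted ALG−AG difference with its 95% confidence interval.

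Analyse M2 in the same way as a secondary comparison. For the cessation objective, keep a within-group M1-to-M2 contrast and its between-arm difference; the mixed model gives both. The 2×3 ANOVA may stay as a description of within-group change, but should not carry the between-arm inference.

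The cost is one degree of freedom and a change of wording. It needs no new data or participants, and the SPSS version already named can fit these models.

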**MOS Short Form Health Survey 36 Item v2 (SF-36 v2).** The SF-36 v2 questionnaire is an assessment tool primarily designed to measure and evaluate the health status and quality of life of populations and individuals, whether they have health conditions or not. It consists of 36 items, rated on a scale from 1 to 5 (Likert scale). The questionnaire is divided into 8 dimensions (physical functioning, physical role limitations, bodily pain, general health perceptions, energy/vitality, social functioning, emotional role limitations and mental health), which can be grouped into two components (physical health and mental health). Scores for each dimension are presented on a positively oriented scale from 0 (worst health state) to 100 (best health state) [78]. The instrument was previously validated and translated for the Portuguese population, demonstrating good content validity (*r*>0.401) and moderate to excellent levels of internal consistency (Cronbach’s α = 0.60–0.87) and test-retest reliability (ICC = 0.45-0.84) across its various domains [79,80]. For this instrument, the MCID has been established at 6 for mental health and 14 for physical health [81].

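### Three unranked primary instruments share a Bonferroni rule with no stated family, while the sample size is for one unspecified VAS test at the full 0.05

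*Protocol article*

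**What the plan says.** **Primary outcomes.** The section of that name covers three instruments, with no order among them and no statement of which decides the trial. They yield different numbers of scores:

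- VAS is recorded three times per visit. Data Collection has "the Visual Analog Scale for pain at rest, during movement, and at night".
- ODI is a single percentage.
- For SF-36 v2, "The questionnaire is divided into 8 dimensions", each scored 0 to 100. The dimensions can be grouped into a physical and a mental component, and the section gives an MCID for physical health and one for mental health.

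**Sample size (Participants).** The calculation concerns one endpoint: "The aim was to detect differences in pain intensity (VAS) between the aquatic exercise program group and the control group (land exercise"). It was run "with an effect size of 1.079, α=0.05, and a power of 80" per cent, and concludes: "The total sample size needed to achieve the objective will be 30 participants (15 in each group").

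**Statistical analysis.** A 2×3 ANOVA is planned for comparisons within and between groups. The next sentence says that "multiple comparisons will be adjusted using the Bonferroni correction (i.e., alpha level divided by the number of tests"). The section later fixes a level of 0.05 ("Significance level set at" that value). It also gives another a priori power calculation, for a repeated-measures interaction with f = 0.4, alpha 0.05 and power 0.95.

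**Time points.** The Introduction puts the effect of stopping training, assessed four weeks after the intervention (M2), among the secondary objectives.

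**The concern.** Dividing alpha by the number of tests is a usable rule only if the number is known. Here it is not given, and the text does not say whether the tests counted are the primary scores, the follow-up contrasts within one ANOVA, or both. Each reading has a cost. If alpha is shared among the primary scores, the trial no longer has the power for which it was sized. If it is not, each primary score is tested at 0.05, and a positive claim can rest on whichever score happens to cross the line.

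The protocol's own Discussion shows that the choice of score can decide the result. In the 65-participant trial used for sizing, ODI and two SF-36 domains differed between groups, while the three VAS scores and the remaining SF-36 domains did not. The Discussion also expects only some SF-36 domains to respond in this trial. With no deciding score named, a reader cannot tell a planned confirmatory result from a selected one.

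**Working it through.** **1. Count the primary scores**

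- VAS 3 + ODI 1 + SF-36 components 2 = 6
- VAS 3 + ODI 1 + SF-36 dimensions 8 = 12
- With dimensions and components = 14
- One score per instrument = 3, the smallest family that keeps all three instruments primary

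**2. Reproduce the stated sample size**

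Inputs from Participants: d = 1.079, alpha = 0.05, power 80%, two equal groups. Sidedness is not stated.

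Two-sample t-test with n per group: df = 2n − 2, noncentrality = d × √(n/2), power = P(|T| > critical t).

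- n = 15: df = 28, noncentrality = 1.079 × √7.5 = 2.955, two-sided critical t at 0.05 = 2.048, power = 81.4%.
- n = 14: power = 78.5%.

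So 15 is the smallest n per group that reaches 80%. A one-sided 0.05 test would need only 12 per group. The stated 30 is therefore right for one two-sided test with no division of alpha.

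**3. Bonferroni across the primary scores**

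Same formula, with alpha = 0.05/k:

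| Tests k | Alpha per test | Critical t (df 28) | Power at 15 per group | n per group for 80% |
|---|---|---|---|---|
| 1 | 0.0500 | 2.048 | 81% | 15 |
| 3 | 0.0167 | 2.546 | 66% | 20 |
| 6 | 0.0083 | 2.839 | 55% | 23 |
| 12 | 0.0042 | 3.120 | 45% | 26 |
| 14 | 0.0036 | 3.181 | 43% | 27 |

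The 15% dropout allowance (about 18 per group) does not close the gap even if nobody drops out: 76% at k = 3 and 57% at k = 12.

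**4. Bonferroni only within each ANOVA**

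Each primary score then has its own 0.05. For independent scores, the chance of at least one false positive is 1 − 0.95^k:

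- k = 3: 14%
- k = 6: 26%
- k = 12: 46%

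The scores will be correlated. The protocol reports ODI–SF-36 correlations of 0.59 to 0.75 in absolute value. Assume that all scores are equally correlated at 0.6 to 0.75 and that the test statistics are jointly normal. Family-wise error is then 19% to 15% for k = 6 and 28% to 21% for k = 12. At an assumed 0.9, the figure for k = 12 is still 13%.

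**5. The second power calculation**

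The Statistical analysis section gives no resulting N and no correlation among repeated measures. The interaction test was computed with noncentrality f² × N × 3/(1 − ρ) and degrees of freedom 2 and 2(N − 2).

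- At an assumed ρ = 0.5, 95% power needs 18 participants in total, not 30.
- At N = 30 and alpha = 0.05/12, power is 97% (ρ = 0.5), 87% (ρ = 0.3) or 67% (ρ = 0).

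This calculation is also for one test at 0.05. It differs from the Participants calculation in test, effect size and power.

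**The case against.** **Bonferroni may concern only the follow-up contrasts.** The sentence comes directly after the 2×3 ANOVA, so this is a natural reading. On it, 0.05 is simply the level being divided, and the 80% is correct for the one VAS comparison it describes. This stands as a possible reading, and it removes the power loss. It leaves the primary scores without any control of error across them, and the VAS score unnamed.

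**The family could be set in a statistical analysis plan that is not shown.** A plan could define it. But if it divides alpha across the primary scores, it contradicts the power in Participants. Which outcome carries the power statement is a protocol matter.

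**The loss of power depends on the calculation used.** This stands. The 66%, 55% and 45% belong to the t-test calculation, which is the one tied to 30 participants. On the repeated-measures basis the loss could be small, depending on an unstated correlation.

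**Stronger readings that the document does not support.** A reader might infer that:

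- all three instruments have several scores; ODI has one;
- there are at least 12 primary scores; testing only the two SF-36 components gives 6;
- M2 competes with M1 as the primary time point; the Introduction makes the cessation question secondary, so M1 is implied;
- the false-positive risk is 46%; that is the independence figure for 12 scores, and the protocol's own correlations point lower;
- the Bonferroni sentence should be deleted; it is the only stated control for the contrasts within each ANOVA.

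**Success might require every primary score to be significant.** No division of alpha would then be needed. The document does not state such a rule, and 80% for one VAS test would still not be the power of that trial.

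**Conclusion.** The point holds in this limited form. The protocol does not say which primary score its power statement concerns or what the Bonferroni rule covers, and neither reading delivers both the stated 80% and control of error across the primary outcomes. This is true for any family larger than one, so it does not depend on whether the count is 3, 6 or 12.

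On the Participants basis the stated 80% becomes 66% to 45%. Without control across scores, the nominal 5% becomes 14% to 46% under independence, or about 15% to 28% for 6 to 12 scores at assumed common correlations of 0.75 to 0.6. The power figures assume d = 1.079, a two-sided t-test and 15 analysed per group. The effect size is taken as stated; nothing here confirms it. The two power calculations also remain unreconciled.

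This should be settled before analysis because it determines what the trial can claim.

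**What to change.** Before analysis and unblinding:

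1. Name one primary score and contrast at M1, ALG against AG, tested at two-sided 0.05. VAS at rest is one defensible choice because it is already the entry variable. State that the 80% power applies to that test only, under the assumed d = 1.079.
2. Make ODI and the two SF-36 components key secondary endpoints, tested by Holm or in a fixed order. Report the other VAS scores, the SF-36 dimensions, TSK-13, MMST and all M2 results as supportive estimates with 95% confidence intervals.
3. Keep Bonferroni, but state that it applies to the follow-up contrasts within each ANOVA.
4. If all three instruments are to stay primary, state the family and the number of tests and restate the power at that alpha. With one score per instrument, that is 66% at 0.05/3 with 15 per group.
5. Reconcile the two power calculations: say which one justifies 30 participants, and give the missing correlation if the repeated-measures one is kept.

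**Cost.** No new data are needed. Either ODI and SF-36 lose co-primary status, although the aim names pain, disability and quality of life together, or the stated power becomes less favourable. Data collection began in November 2024, so the change must be documented, in the protocol and the registry, as made after that date.
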